## Abstract

**Background:**

Depression and anxious symptoms are prevalent in the general population, and their onset and persistence may be linked to biological and psychosocial factors, many of which are lifestyle-related. The way we manage our care, physical and emotional health and/or discomfort is highly influenced by our own abilities, skills and attitudes despite life’s circumstances. The main aim of this protocol to analyze the relationship between psychological constructs (self-efficacy, activation, health literacy, resilience, personality traits, sense of coherence, self-esteem), and the presence of affective-emotional problems (anxiety, depression) and addictions in primary health care.

**Methods:**

This is a protocol of a prospective longitudinal cohort study including people of 35–74 years old of Aragon primary health care centers (Spain). Three evaluations will be conducted: baseline evaluation, and follow-up assessments five and ten years after recruitment. The primary outcomes will be severity of depression, severity of anxiety, and addictive behaviors. A detailed set of secondary outcomes will be assessed across all three assessments. This will include psychosocial or personal factors on health behavior, social support, lifestyle patterns, quality of life, the use of health and social resources, and chronic comorbid pathology.

**Discussion:**

The analysis of the impact of psychological constructs and lifestyles on the mental health of people and communities will provide evidence that will make it possible to better address and prevent these prevalent problems and address their improvement from a more global and holistic perspective. The evaluation of psychological constructs should be incorporated into health services to improve people’s ability their self-care, the level of knowledge of managing their disease and their physical, mental and social health.

**Clinical trial registration:**

https://www.isrctn.com/, identifier ISRCTN12820058.

## 1. Introduction

Affective disorders are a relevant and growing health problem, with a significant level of morbidity worldwide (1). In 2017, the World Health Organization reported that 4.4% of the world’s population suffered from depression and 3.6% from anxiety. These disorders are more prevalent in women than in men (depression: 5.1% vs. 3.6; anxiety 4.6% vs. 2.6%, respectively) (2). Currently, the COVID-19 pandemic has had a severe impact on the mental health and wellbeing of the world population, increasing cases of major depression by 27.6% and cases of anxiety disorders by 25.6% (3, 4). In Spanish primary health care (PHC), the most frequently registered mental health problems are anxiety disorder (6.7%), and depressive disorder (4.1%) (5). Addictive behaviors are another relevant mental health problem in PHC (6). 33.1% of the population aged 15–64 years consume tobacco daily, while daily alcohol consumption stands at 9.0% (7). Finally, 3.5% of the same population engages in compulsive use of the Internet and 2.8% consumes cannabis daily (7, 8).

According to the International Classification of Diseases 11th, depression, anxiety, and addictive behavior disorders are mental, behavioral, or neurodevelopmental disorders (9). These syndromes are characterized by a clinically significant alteration in the cognition, emotional regulation, or behavior of an individual (9). Moreover, they are the result of complex interactions between social, psychological, and biological factors and are generally associated with significant distress or impairment in personal, family, social, educational, occupational, or other important areas of functioning (10). It must be considered that any mental health problem is a serious health problem when it is of long duration, of at least moderate-severe intensity, and alters the conciliation and daily life (11, 12).

The way we manage our care, physical and emotional health and/or discomfort is highly influenced by our own abilities, skills and attitudes regardless of life circumstances (13, 14). Some of these factors are health literacy (15), patient activation (16), self-efficacy (17), resilience (18), sense of coherence (19), self-esteem (20), and personality characteristics (21). First, the level of health literacy is defined as the knowledge of the population, their motivation and individual abilities to understand and make decisions related to the promotion and management of their health (15). In recent evidence, health literacy interventions improve the emotional state of patients in primary care, with a moderately positive effect on reducing depression and anxiety symptoms (22). Second, self-efficacy is represented as a feeling of confidence in one’s abilities to deal with certain stressors in life (17). Increased self-efficacy beliefs have also been connected to improved emotion management and psychosocial functioning (23, 24). Moreover, low self-efficacy is related, for example, to depression, alcohol use and internet addiction (25–27). Third, resilience represents as a positive adaptation to adversity, such as misfortunes and adverse life events (18). Low resilience has been associated with high levels of depression, addictive behavior, anxiety, and mortality (28–30). Encouraging high resilience in subjects has been found to be an effective method to minimize addictive Internet usage (31, 32). Fourth, sense of coherence is defined as the personal attitudes to the values of vital experiences (19). Some data show a positive relationship between an improved sense of coherence and lower levels of depression, anxiety, and problematic use of the Internet (33, 34). Fifth, self-esteem is represented as a positive or negative feeling about oneself and is constructed through the evaluation of one’s own attributes (20). Adults with higher overall self-esteem are more likely to experience physical, mental, professional and social well-being. For example, low self-esteem is associated with behavioral addictions such as emotional problems, substance abuse, and problematic use of new technologies (35, 36). Finally, the personality traits that influence mental health and addiction include introversion, low conscientiousness, neuroticism, low agreeableness, and low openness (37). Those with much higher neuroticism scores and lower extraversion and conscientiousness scores had higher anxiety and depressive symptoms (38). Addiction to new technologies is associated with adults with personality traits such as neuroticism, openness, and low conscientiousness (39, 40).

Furthermore, the onset and persistence of affective disorders has been associated with specific lifestyle characteristics (e.g., poor-quality diet, sleep disturbances, and sedentary lifestyle) (41–43). Therefore, some healthy habits (e.g., good nutrition, quality sleep, sufficient physical activity) are associated with lower levels of depression and anxiety (44, 45). In particular, improving physical activity has a moderate to large effect on improving depressive symptoms (46). Additionally, depression severity and current depression diagnosis are associated with unhealthy dietary intake and poorer food quality (47). Moreover, sleep disturbances increase the risk of suicidal behavior in depressed patients (48). Furthermore, addictive behaviors (e.g., tobacco use, harmful use of alcohol, substance abuse, and compulsive use of the Information and Communications Technologies (ICT) can coincide with, contribute to, or result from mental disorders such as depression or anxiety (49–51). Current evidence suggests the high probability of exacerbation of anxious or depressive disorders when they coexist with chronic comorbidities (52). Several studies have found that people with chronic diseases have a higher risk of developing mental disorders such as depression or anxiety (52–54). Simultaneously, people diagnosed with a mental health disorder are more likely to have chronic physical conditions than a person without a mental health diagnosis (52, 55). Moreover, a prospective cohort study of community individuals with a follow-up after 11 years indicated that the increase in depressive symptoms over time was associated with higher mortality rates (56).

Mental health disorders generate a great economic burden in the use of health system services and represent a significant proportion of health-seeking contacts in primary care (57, 58). In Spain, around 70–85% of the population opts for public primary health care over private insurance (59). Specifically, 60% of frequent users in primary health care suffer from some mental health problem, particularly depressive or anxiety disorders (60). Only 10% of patients with mental health problems seen in primary care are referred to mental health units (61). A World Health Organization report highlights the fundamental role of PHC personnel in the detection, diagnosis, and treatment of people with mental disorders (62, 63). The importance of the PHC lies in being the gateway to the health care system, its accessibility and its interaction with people with mental health problems and their families (61). Most people with mental health problems access primary care, and their disorders are more likely to be identified and treated appropriately and with less risk of stigma (62). In addition, the integration of mental health into primary care promotes comprehensive, coordinated, and person-cantered care for the many people with co-morbid physical and mental health problems (62).

Promoting the participation of the population in coping with diseases and their self-care and self-management of health is a key element in the health of the population in general and especially of the population with affective disorders (64). It is necessary to investigate further how people’s psychological constructs, beliefs and self-care capacity, as well as their lifestyles, can affect the well-being or discomfort of people and contribute to a healthier life from the perspective of mental health. Furthermore, it is important to assess longitudinal changes in these factors and affective disorders given their association with increased comorbidity and mortality (56). The analysis of the impact of psychological constructs and lifestyles on the mental health of individuals and communities will provide evidence that will make it possible to better address and prevent these prevalent problems as well as foster their improvement from a more global and holistic perspective.

Our main objective in this study is to analyze the relationship between psychological constructs (self-efficacy, activation, health literacy, resilience, personality traits, sense of coherence, self-esteem), affective-emotional problems (anxiety, depression) and addiction in primary health care. Therefore, our main hypothesis is that subjects with lower levels of the psychological constructs (self-efficacy, activation, health literacy, resilience, sense of coherence, self-esteem) will have more severe depressive, anxious, and addictive behavior symptoms than those with higher values of the psychological constructs.

One of the secondary objectives of this study is to analyze whether these psychological constructs act as mediating or moderating factors in the relationship between the diagnosis of comorbidities or healthy lifestyles and depression, anxiety, and addictive disorders. Therefore, our secondary hypothesis is that the relationship between the diagnosis of comorbidities or healthy lifestyles and depression, anxiety, or addictive disorders will change according to the value of the different moderators, such as self-efficacy, activation, health literacy, resilience, personality traits, sense of coherence, and self-esteem.

Moreover, a final secondary objective is to create a cohort for an analysis of the relationship between these psychological constructs and lifestyles and the incidence rate of diagnoses of depression and/or anxiety to be revisited after 5–10 years. Consequently, our last secondary hypothesis is that people with lower levels of the psychological constructs and less healthy lifestyle habits will be more likely to experience increased incidence of diagnoses of depression and anxiety or worsening symptoms in the following 5 to 10 years than will those with higher values of the psychological constructs of healthy lifestyles.

## 2. Materials and methods

### 2.1. Study design

This study is a protocol of a prospective longitudinal cohort study. This study will be the first baseline measurement for creating a cohort with expected follow-up at 5–10 years. According to current evidence from prospective studies in the community population (56), and the advantages of a cohort study, follow-up at 5–10 years will make it possible to determine incidence, natural history, clinical course, and assess mortality (65). This protocol was registered with ISRCTN Registry before commencement (ISRCTN12820058). For the creation of this protocol, we followed the standard protocol items: recommendations for interventional trials (SPIRIT) guidance (Supplementary Material 1), and the study will be performed and reported according to the guidance for strengthening the reporting of observational studies in epidemiology (STROBE).

### 2.2. Contextual framework

The study will be carried out within the framework of primary health care in the Spanish region of Aragon. Aragon is an Autonomous Community located in the northeast of Spain. It is the fourth Spanish Autonomous Community by territory but ranks 11 out of 17 in terms of population. It has a population of 1.3 million inhabitants: 60% live in urban areas (675,301 inhabitants live in the city of Zaragoza) and semi-urban areas and 40% of the remaining population lives in towns with fewer than 5,000 inhabitants. Aragon has an aging population, with 23.5% of people over 64 years of age. The average socioeconomic level of Aragon is medium, and the unemployment rate is lower than the national average. Public health provides assistance for nearly the entire population [around 70–85% of the population opts for public primary health care over private (59)]. Aragon public primary health care is structured into 8 health sectors organized into 123 Basic Healthcare Areas (BHA), which include 118 health centers and 870 local clinics (66, 67). Spanish primary health care is made up of a multidisciplinary team of general practitioners, nurses, psychologists, social workers, physiotherapists and occupational therapists.

### 2.3. Inclusion and exclusion criteria

The inclusion criteria are (A) participants of 35–74 years old; (B) ability to speak and write in Spanish; (C) ability to understand the study and provide consent to participate in the study voluntarily. According to national clinical data from Primary Care, the most frequent stage of onset of depression and anxiety is the decade between 30 and 40 years of age. At this age, these disorders are more prevalent in women than in men (depression: 4.2% vs. 2.0%; anxiety: 10% vs. 5.7%, respectively) (5). In addition, in this age range, these affective disorders have a notable impact on people who are usually at the age of full work, economic and family activity (68). The prevalence of these pathologies increases with age, decreasing slightly from the age of 75, and the trend of higher prevalence in women than in men continues to increase with age (depression: 12.2% vs. 4.8%; anxiety: 11.3% vs. 5.0%, respectively) (5).

The exclusion criteria are (A) suffering from a terminal illness; (B) being institutionalized at the time of the appointment; (C) difficulty participating due to cognitive dysfunction, dementia, or any serious disease that may seriously interfere with the patient’s participation in the study; (D) persons who plan to move out of Spain within five years after the initiation of the study.

### 2.4. Sample size and sampling

The sample size was computed using the formula for caclulating the population estimates of the most prevalent affective disorders in primary care (anxiety and depression) (69). To calculate the sample size, we will use the data obtained in the study by Santomauro et al. (57). We used the prevalence of the most frequent affective disorders and addictions in primary care (anxiety, depression) as the main variable: 3.1% for major depression and 4.8% for anxiety disorders. Accepting an alpha value of 0.05 and a margin of error of 3% of units, the total sample size required was 290 with the expectation of a possible 30% withdrawal rate.

n=Zα2⁢p⁢(1-p)e2

For selecting potential participants, stratified selection will be made by age, sex and population distribution in urban and rural areas with respect to the National Institute of Statistics data from the census of Aragon 2021 (Figure 1 and Table 1). This stratification will be carried out with the intention of establishing the greatest variability within the sample and reaching a maximum level of representativeness for the population (Table 2). To achieve this, different primary care health centers in the autonomous community, 1–2 rural centers and 1–2 urban centers, will be selected. The rural centers sampled will be in towns with a population of under 2,000 inhabitants.

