#### 2.6.1. Primary outcomes

The main variables will be severity of depression, severity of anxiety, and addictive behaviors.

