### 2.7. Data analysis

Baseline analysis of the results: Descriptive analysis of all variables (percentage and confidence interval for qualitative variables; means and standard deviation for parametric quantitative variables or median and interquartile range for non-parametric quantitative variables) and univariate analysis (we will use the T-Student for parametric quantitative variable, Mann-Whitney U for non-parametric quantitative variables, and the Chi-Square test for qualitative variables) to evaluate the differences between the patients who have some of the most prevalent affective-emotional problems in primary care (anxiety, depression) compared with those who do not. Statistical analyses will be chosen based on the size of the sample (parametric or non-parametric tests). To compare the two groups, missing data will be assessed and the need to use an intention-to-treat (ITT) analysis and a multiple imputation (MI) technique to handle missing data will be assessed.

To answer the main objective, we will use a multiple linear regression model. To do this, each main variable, the PHQ-9 score, BDI-II, GAD-7, PGBQ, AUDIT, and MULTICAGE-ICT, will be used as a continuous variable. Multiple linear regression will be performed using a stepwise method to obtain a better fit result to the statistical analysis. This stepwise regression simply will repeat the multiple regression, each time removing the least correlated variable. Only the significant variables obtained in the bivariate analysis will be entered into the regression model.

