Finally, mediation/moderation analyses will be carried out to analyze whether psychological constructs participate as a mediator or as a moderator in the association of lifestyles (exposure) and anxiety, depression and/or addictions (outcome). The PROCESS analytical tool developed by Hayes will be used to assess mediation/moderation. These analyses were based on multiple linear regression path analysis (93). Bootstrap resampling (10.000 samples) will be used to estimate 95% confidence intervals. Given that heteroscedasticity is common in cross-sectional data, all analyses will include a correction for heteroscedasticity (HC0) (94). The Johnson-Neyman technique will be used to compute the range of significance and simple slopes for the interaction analyses (93). We will report unstandardized regression coefficients; all analyses will be two-tailed and used conventional significance thresholds (α = 0.05). Data collection and statistical analysis will be performed using Excel software, SPSS software (version 25.0) (95) and the statistical software environment R (version 3.6.2) (96).

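### The figure of 290 is derived for the precision of a prevalence, but the main objective is a regression of continuous scores on psychological constructs, so 290 is not justified for that objective

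*Protocol article*

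**What the plan says.** Section 2.4 (Sample size and sampling) prints the precision formula for a single proportion and states: "We used the prevalence of the most frequent affective disorders and addictions in primary care (anxiety, depression) as the main variable". The inputs are "3.1% for major depression and 4.8% for anxiety disorders" and "Accepting an alpha value of 0.05 and a margin of error of 3% of units". The result is that "the total sample size required was 290 with the expectation of a possible 30% withdrawal rate". Addictions are named, but no addiction figure is given. Table 2, in the same section, shows a stratified selection totalling 395.

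Other sections set a different target:

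- Introduction: "Our main objective in this study is to analyze the relationship between psychological constructs", affective-emotional problems and addiction. The main hypothesis is directional: lower construct levels go with more severe symptoms.
- Section 2.6.1: "The main variables will be severity of depression, severity of anxiety, and addictive behaviors".
- Section 2.7: "To answer the main objective, we will use a multiple linear regression model". The PHQ-9, BDI-II, GAD-7, PGBQ, AUDIT and MULTICAGE-ICT scores each enter as continuous outcomes.

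Recorded psychological comorbidities come from the electronic medical record and are listed among the secondary outcomes (section 2.6.2.1).

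**The concern.** The protocol names two different main variables. One is a prevalence, which sets the sample size. The other is a set of scores, which the main analysis uses. A margin of 3 percentage points on a prevalence cannot be converted into the precision of a regression coefficient: the calculation contains no effect size, residual variance, number of predictors, correlation among predictors or power.

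A reader who sees a required sample size of 290 will take it as support for the main hypothesis. It says nothing about how precisely the relation between, say, self-efficacy and PHQ-9 will be estimated. When results arrive, nothing in the plan will help a reader judge whether a non-significant construct reflects a weak relation or a wide interval.

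**Working it through.** **1. Where 290 comes from.** Inputs from section 2.4: p = 0.031 and 0.048, margin e = 0.03, alpha 0.05, withdrawal 30%. Section 2.7 states two-tailed analyses, so z = 1.96. The printed formula is n = z² p(1−p)/e², followed by division by 0.70.

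| p | n before loss | n / 0.70 |
|---|---|---|
| 0.031 (stated) | 3.8416 × 0.030039 / 0.0009 = 128.2, so 129 | 185 |
| 0.048 (stated) | 3.8416 × 0.045696 / 0.0009 = 195.0, so 196 | 280 |
| 0.05 (not stated) | 3.8416 × 0.0475 / 0.0009 = 202.7, so 203 | 290 |

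The stated inputs give 280 at most. The figure 290 appears if 4.8% is rounded up to 5%. That rounding is an inference, but it leaves little doubt that 290 is a prevalence-precision number and that nothing about the regression entered it.

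**2. The two targets side by side.**

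| | Section 2.4 | Introduction, 2.6.1, 2.7 |
|---|---|---|
| Main variable | prevalence of disorders | severity and addiction scores |
| Scale | proportion | continuous |
| Aim | estimate within 3 points | association with constructs |
| Method | single-proportion formula | multiple linear regression |

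None of the objectives in the Introduction is to estimate prevalence. The nearest is the secondary objective on incidence of diagnoses over 5 to 10 years.

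**3. What the numbers would deliver for the main objective (illustration).** The documents give no inputs for this, so the following are assumptions:

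- 11 construct scores in a fixed model: self-efficacy, resilience, sense of coherence, self-esteem, activation, health literacy and five personality factors.
- Outcome R² = 0.30.
- R² of one construct on the others, R²x, between 0.3 and 0.6. Variance inflation is 1/(1−R²x), that is 1.4 to 2.5.

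SE(standardised coefficient) = √[(1 − 0.30) / ((n − 12)(1 − R²x))], and half-width = 1.96 × SE.

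- n = 290, R²x = 0.3: √[0.70/(278 × 0.70)] = 0.060; half-width 0.118.
- n = 290, R²x = 0.6: √[0.70/(278 × 0.40)] = 0.079; half-width 0.156.
- n = 395, R²x = 0.3: √[0.70/(383 × 0.70)] = 0.051; half-width 0.100.
- n = 395, R²x = 0.6: √[0.70/(383 × 0.40)] = 0.068; half-width 0.133.

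For follow-up analyses after 30% loss, 290 becomes 203 (half-width 0.14 to 0.19) and 395 becomes about 276 (0.12 to 0.16).

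**4. Cross-check by power.** A noncentral F test of one coefficient (two-sided alpha 0.05, 80% power, 11 or 20 predictors) gives these smallest detectable effects:

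- n = 290: partial f² = 0.027, partial r about 0.16.
- n = 395: partial f² = 0.020, partial r about 0.14.
- n = 203: partial f² = 0.039, partial r about 0.19.

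**The case against.** **Proportions are not foreign to this study.** The abstract words the aim partly in terms of the presence of affective problems. A secondary objective concerns incidence of diagnoses. Section 2.7 plans percentages with confidence intervals and a comparison of patients with and without anxiety or depression. This stands as far as it goes, and it is why the prevalence margin may be kept as a secondary statement. But the comparison is part of the baseline univariate step, and section 2.7 assigns the main objective to linear regression on scores.

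**The study may well be large enough.** This also stands. A reader might infer that the design can see only moderate effects. The figures do not support that: f² of 0.027 at 290, or 0.039 at 203, lies nearer the conventional small value (0.02) than the medium one (0.15).

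**The loss-adjusted number may not apply.** Section 2.7 opens as a baseline analysis, and section 3.1 links withdrawal to refusal to complete follow-up. The figures at 203 or 276 therefore belong to follow-up analyses only.

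**The illustrated model is not the planned one.** Section 2.7 enters only variables significant in bivariate analysis and then removes variables stepwise. The half-widths above assume a fixed model, so they are illustrative. Precision can be stated properly only for a pre-specified model.

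**Questionnaire cut-offs.** A reader might infer that prevalence will be read from the severity bands and so miss the 3-point margin through misclassification. No section plans such an estimate; the main analysis uses the scores as continuous variables.

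**Conclusion.** The point holds as a mismatch between the basis of the sample size and the main analysis. Section 2.4 is wrong as written in calling prevalence the main variable, and 290 is not justified for the main objective. It does not follow that 290 is too small, and nothing here calls for more participants.

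Under the assumptions shown, the precision the plan leaves unstated is a half-width of about 0.12 to 0.16 for a standardised construct coefficient at 290, and about 0.10 to 0.13 at 395. These ranges rest on an assumed R² of 0.30, 11 scores in a fixed model and variance inflation of 1.4 to 2.5; none of these comes from the documents. The textual contradiction does not depend on any of them.

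**What to change.** In section 2.4:

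1. Remove the statement that prevalence is the main variable.
2. State one planned number. Reconcile 290 with the 280 that follows from 4.8% and 30% loss, and with the 395 in Table 2.
3. State what that number delivers for one construct coefficient in a pre-specified PHQ-9, BDI-II or GAD-7 model: the expected confidence interval half-width, with the assumed R², number of predictors and variance inflation shown. Give the number after 30% loss for follow-up analyses only.
4. Keep the prevalence margin, if wanted, as a secondary statement tied to diagnoses in the medical record.

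The cost is a rewritten paragraph and agreement on one number and one model. Enrolment and data collection need not change. The downside is that the stated precision will look less favourable than the present 3-point margin suggests.

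### The sample size of 290 does not follow from the stated prevalences, and the anxiety prevalence used is below the protocol's own Spanish primary-care figures

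*Protocol article*

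**What the plan says.** Section 2.4 says that the sample size serves "population estimates of the most prevalent affective disorders in primary care (anxiety and depression". It applies n = Z²p(1−p)/e² and gives the prevalences as "3.1% for major depression and 4.8% for anxiety disorders", taken from one cited study and described as primary-care values. The other settings are "Accepting an alpha value of 0.05 and a margin of error of 3% of units". The result is that "the total sample size required was 290 with the expectation of a possible 30% withdrawal rate".

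The protocol gives Spanish primary-care figures in two other places:

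- The Introduction reports "anxiety disorder (6.7%), and depressive disorder (4.1"%.
- Section 2.3 cites national primary-care data, women against men. For the decade from 30 to 40 it gives "depression: 4.2% vs. 2.0%; anxiety: 10% vs. 5.7%, respectively". For later ages, with no band stated, it gives "depression: 12.2% vs. 4.8%; anxiety: 11.3% vs. 5.0%, respectively".

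Table 2 allocates 395 people (198 men, 197 women). The text does not say how 395 relates to 290.

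**The concern.** Two things look wrong. First, putting the stated inputs into the stated formula does not return 290. Second, every anxiety figure the protocol reports for Spanish primary care is above 4.8%; the lowest is the 5.0% for men at later ages. At these prevalences p(1−p) grows with p, so too low a prevalence makes the sample look more precise than it will be.

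This calculation is the only justification given for the size of the cohort. A reader cannot tell which prevalence was used, whether the margin applies before or after withdrawal, or whether the plan is for 290 or 395 people.

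**Working it through.** **Inputs.** Z = 1.96 (alpha 0.05, two-sided), e = 0.03 (reading "a margin of error of 3% of units" as 3 percentage points) and 30% withdrawal, all from section 2.4. Prevalences are from section 2.4, the Introduction and section 2.3. The 395 is the Table 2 total.

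**Step 1: reproduce 290.** Evaluable n = 1.96² × p(1−p) / 0.03²; recruited n = evaluable n / 0.70. The lower figure of each range comes from rounding to nearest, the upper from rounding up at each step.

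| p | Evaluable n | Recruited n |
|---|---|---|
| 3.1% (stated, depression) | 128.2, so 128–129 | 183–185 |
| 4.8% (stated, anxiety) | 195.0, so 195–196 | 279–280 |
| 5.0% (not stated) | 202.7, so 203 | 203/0.70 = 290 |

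Other readings do not give 290 either. Inflating by × 1.3 gives 255 at 4.8% and 168 at 3.1%. A one-sided Z at 4.8% gives 138, or 198 after loss. Summing the prevalences (7.9%) gives 311, or 445 after loss. The likely explanation is that 4.8% was rounded to 5%.

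**Step 2: the protocol's own anxiety figures.** Overall: 6.7%. Table 2 has almost equal numbers of men and women, so I take simple means of the sex-specific rates:

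- Age 30–40: (10 + 5.7)/2 = 7.85%.
- Later ages: (11.3 + 5.0)/2 = 8.15%.

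Using these for ages 35–74 is my assumption.

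For depression the corresponding values are 4.1% overall, (4.2 + 2.0)/2 = 3.1% at 30–40, and (12.2 + 4.8)/2 = 8.5% at later ages.

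**Step 3: margin delivered.** Margin = 1.96 × √(p(1−p)/N), in percentage points. N is 290 × 0.70 = 203, 395 × 0.70 = 276 (rounded down), 290 or 395.

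| p | N = 203 (290 after loss) | N = 290 | N = 276 (395 after loss) | N = 395 |
|---|---|---|---|---|
| Anxiety 4.8% (plan) | 2.94 | 2.46 | 2.52 | 2.11 |
| Anxiety 6.7% | 3.44 | 2.88 | 2.95 | 2.47 |
| Anxiety 7.85% | 3.70 | 3.10 | 3.17 | 2.65 |
| Anxiety 8.15% | 3.76 | 3.15 | 3.23 | 2.70 |
| Depression 3.1% | 2.38 | 1.99 | 2.04 | 1.71 |
| Depression 4.1% | 2.73 | 2.28 | 2.34 | 1.96 |
| Depression 8.5% | 3.84 | 3.21 | 3.29 | 2.75 |

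The highest prevalence at which 3 points is still met is 5.0% with 203, 6.9% with 276, 7.3% with 290 and 10.3% with 395.

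**Step 4: numbers needed for 3 points.** At 6.7%: 267 evaluable, or 381–382 recruited with 30% loss. At 8.15%: 320 evaluable, or 457–458 recruited.

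**The case against.** The strongest reply is that prevalence is measured at baseline. Section 2.1 presents this study as the first baseline measurement, and section 3.1 describes withdrawal as refusal to complete follow-up. Everyone assessed at baseline would then count. With 290 assessed, the margin is 2.88 points at 6.7%, which meets the target, and about 3.1 at 8%, a miss of roughly 0.1 point. With 395 assessed, the target is met at every overall or sex-averaged prevalence used here. This stands, and it removes the tempting reading that 290 simply fails to deliver 3 points. The clear miss depends on counting 203, which is how section 2.4 itself builds the withdrawal into 290.

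A reader might also infer that depression is under-sized. The documents do not support that as a general statement: 4.1% is covered in every scenario, and the 30–40 sex mean equals the 3.1% used. Only the later-age mean of 8.5% exceeds what the plan covers. Nor does a prevalence of 3.1% come with a margin as wide as itself: the delivered margin there is 2.4 points or less.

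Three further points have weight. The source behind 3.1% and 4.8% may define cases differently from disorders registered in primary care, so choosing it is partly judgement; but section 2.4 does not give that reason. Rounding 4.8% up to 5% is conservative, since 290 exceeds 279–280. And the main objective concerns associations, analysed by linear regression on continuous scores (section 2.7), so no stated hypothesis turns on a 3-point prevalence margin. These points limit the consequence. They do not make the figure reproducible or explain the gap between 290 and 395.

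**Conclusion.** The point holds as a defect in the stated sample-size justification. 290 follows from neither stated prevalence and needs an unstated 5.0%. The anxiety input is below every Spanish primary-care anxiety figure in the protocol, and no reason is given.

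The effect on precision is modest and conditional. For anxiety at 6.7% to about 8.2%, the margin is 3.4–3.8 points with the 203 left after loss, so the target is missed by 0.4–0.8 point. With all 290 assessed it is met at 6.7% and narrowly missed at about 8%. With 395 it is met before loss; after loss it is met at 6.7% (2.95) and missed by about 0.2 point at 8%.

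This rests on reading the margin as percentage points and on the simple formula in section 2.4. The values around 8% also assume equal weighting of the sexes and that two age snapshots stand in for ages 35–74. The 6.7% result needs neither of those last two assumptions. The documents do not support concluding that the cohort is too small for its purpose.

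**What to change.** Rewrite the sample-size paragraph in section 2.4 to:

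1. State the prevalence actually used (apparently 5.0%) and justify it against the Spanish primary-care figures in the Introduction and section 2.3, including any difference in case definition.
2. Reconcile the 290 in the text with the 395 in Table 2, saying which is the recruitment target and why they differ.
3. Report the delivered margin separately for anxiety and depression, before and after 30% loss. If 290 is the target, for example: anxiety at 6.7%, 2.9 points before loss and 3.4 after; depression at 4.1%, 2.3 and 2.7. If 395 is the target: anxiety 2.5 and 2.95; depression 2.0 and 2.3. Add anxiety at about 8% and depression at 8.5% as sensitivity values, labelled as derived.

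The cost is one recalculated paragraph and a slightly less favourable stated precision. Recruitment does not need to change.
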